## Data Analysis

Baseline characteristics of participants will be compared between the arms using t-tests for continuous variables and chi-square tests for categorical variables to assess balance across study arms.

Primary Implementation Outcomes: Quantitative measures of feasibility, acceptability, and fidelity will be summarized using means and standard deviations or proportions and compared across arms using statistical models for continuous or binary outcomes, as appropriate. Specifically, we will compare the mean number of people enrolled and the proportion retained in each arm through 6 months (feasibility); the proportion of participants who found the intervention easy to administer and helpful (acceptability), and the proportion of interventionists covering at least 80% of checklist items during random direct monitoring sessions (fidelity). Qualitative measures of acceptability (e.g. open-ended questions on the exit interview) will be analyzed using textual data analysis steps described in Aim 1 (reading for content; coding; data display, data reduction and interpretation).^76,77^

Secondary Preliminary Efficacy: Preliminary efficacy will be analyzed at 2, 4, and 6 weeks and 3 and 6 months and compared between study arms. In addition, statistical models examining differences in prevalence of SIBs, suicide risk, and depressive symptoms will account for baseline values by using generalized estimating equations with an exchangeable correlation matrix. Importantly for the design of the subsequent RCT, this pilot will yield estimates of the within-clinic intra-cluster correlation and the standard deviation for the effectiveness outcomes.

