# METHODOLOGY

## Design of Study

In this randomized controlled pilot trial across five public health clinics, participants will be individually randomized 1:1 either to enhanced FB+SP (N = 30) or augmented usual care (N = 30) and followed for 6 months. Primary and secondary outcomes will be assessed at 2-, 4-, and 6-week; and 3- and 6- month study visits and compared across the two study arms.

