## Sample Size Determination

Trial: We expect to be able to recruit 60 ALWH. The primary goal of this R34 proposal is to evaluate the feasibility, acceptability, and fidelity of the enhanced FB+SP model to address suicidality ALWH. In Aim 2, we will enroll 60 ALWH with SIBs in a 2-arm randomized pilot (30 per arm) to compare augmented usual care with the enhanced FB+SP intervention. Information on preliminary effectiveness of the intervention across a range of mental health outcomes related to SIBs will be assessed, but interpreted cautiously as efficacy is only a secondary aim of this pilot study. Intervention effectiveness will subsequently be assessed in a large-scale R01 clinic-level RCT. The sample of 60 ALWH (30 per arm) will be sufficient to estimate quantitative measures of feasibility and acceptability with reasonable precision (e.g., standard errors of .06-.09 for proportions).

Qualitative Interviews: Some providers involved in the delivery of the FB+SP intervention (N=10) and patients in the intervention arm (N=10) will be asked to complete brief exit interviews at their study sites to assess facilitators and barriers to the delivery and receipt of the FB+SP intervention. As is common in qualitative research, we aim to continue data collection until data saturation has been achieved. Based on prior experiences employing these methods and achieving saturation, this sample size is expected to be sufficient to capture a diverse range of perspectives as well as achieve theme saturation in each group.

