## Data Collection Techniques and Tool

Implementation outcomes: This trial will explore patient and provider ***acceptability*** and ascertain ***feasibility*** of recruitment, retention, and participation. We will conduct audio-recorded semi-structured qualitative interviews with a random sample of patients enrolled in the study (N = 10). Exit interviews will explore acceptability of the intervention to patients (ease of participation or delivery, perceived usefulness of the intervention, suggestions for improvement, and contextual factors that impeded or facilitated implementation). Acceptability will also be assessed quantitatively with the *Client Satisfaction Questionnaire-8*.^57^ Feasibility will be assessed through the number of ALWH enrolled; a comparison of planned relative to actual enrollment; reasons for non-enrollment; the proportion of ALWH retained in each arm; and the number of sessions attended during the study period. Additionally, we will interview clinic staff (N = 10) involved in the delivery and/or supervision of the intervention to assess acceptability to providers and feasibility (perceived changes, comfort level and competency, training satisfaction, recommendations, barriers and facilitators). We will monitor ***fidelity*** to the intervention protocol using the *Fidelity Checklist­* and in-depth interviews with clinic staff (**Table 1**).

Preliminary Effectiveness: This trial will assess patient outcomes as a measure of preliminary effectiveness, comparing the prevalence of SIBs, suicide risk, and depressive symptoms between the two study arms. Patients will be surveyed by the RAs at enrollment (baseline), 2 weeks post-enrollment (FU1), 4 weeks post-enrollment (FU2), 6 weeks post enrollment (FU3), 3 months post-enrollment (FU4), and 6 months post-enrollment (FU5) (**Table 1**). VL draws will occur at enrollment (baseline) and 6 months post-enrollment (FU5). Additionally, RS will abstract clinical data related to ART appointment attendants, providers assessment of patients’ depressive symptom and suicidal ideation and behaviors and continue treatment as clinically indicated.

| **Table 1. Assessment Domains, Constructs, and Measures** | | | | |
| --- | --- | --- | --- | --- |
| **Domain** | **Construct** | **Measures** | **Assessment Point** | **Data**  **Type** |
| **Primary Implementation Outcomes** | | | | |

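### Two of the primary implementation measures cannot be meaningfully compared between arms, a third is undefined for controls, and the patient exit-interview sample is defined in two incompatible ways

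*Protocol*

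**What the plan says.** Section 5.1 sets the design: "participants will be individually randomized 1:1 either to enhanced FB+SP (N = 30) or augmented usual care (N = 30". Table 1 in section 5.6 lists feasibility, fidelity and acceptability as the primary implementation outcomes.

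Section 5.7 states that the quantitative measures of all three will be summarised and compared between arms with models for continuous or binary outcomes. It then names the quantities:

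- Feasibility: "we will compare the mean number of people enrolled and the proportion retained in each arm through 6 months (feasibility".
- Acceptability: "the proportion of participants who found the intervention easy to administer and helpful (acceptability".
- Fidelity: "the proportion of interventionists covering at least 80% of checklist items during random direct monitoring sessions (fidelity".

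Section 5.6 describes fidelity as adherence to the intervention protocol, measured by a checklist. It names the CSQ-8 as the quantitative acceptability measure. For feasibility it already lists actual against planned enrolment, reasons for non-enrolment, retention in each arm and sessions attended.

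On exit interviews, section 5.6 plans "a random sample of patients enrolled in the study (N = 10". Sections 5.3 and 5.4 likewise speak of a random sample of 10 participants without naming an arm. Section 5.5 instead specifies "patients in the intervention arm (N=10".

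**The concern.** Feasibility, acceptability and fidelity are the stated primary goal of the pilot, and its results are meant to shape a later trial. A between-arm comparison informs only if the quantity exists in both arms and can differ because of the allocated care. Number enrolled does not meet the second condition, and checklist fidelity does not meet the first. The acceptability item refers to an intervention that controls do not receive. It also asks about ease of administering, which is a matter for those who deliver the sessions, whereas section 5.6 puts questions of delivery and comfort to clinic staff.

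The interview conflict affects what is collected. The interviews explore acceptability of the intervention, and section 5.5 bases its expectation of saturation on 10 patients from the intervention arm. If staff sample from everyone enrolled, fewer than 10 of those interviewed will have experienced FB+SP.

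**Working it through.** **The plan's own precision figure.** Section 5.5 says the sample "will be sufficient to estimate quantitative measures of feasibility and acceptability with reasonable precision (e.g., standard errors of .06-.09 for proportions". With SE = √[p(1−p)/n]:

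- n = 30, p = 0.50: √(0.25/30) = 0.091
- n = 30, p = 0.87: √(0.1131/30) = 0.061
- n = 60, p = 0.50: √(0.25/60) = 0.065

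The stated range reproduces at n = 30 for p from about 0.50 to 0.88. Moving FB+SP-specific participant measures to a one-arm summary (n = 30) therefore leaves it intact.

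**Enrolment by arm.** Participants enrol and are then allocated 1:1, so the planned difference is 30 − 30 = 0. The protocol does not describe blocking. If simple unrestricted randomisation of 60 is assumed, one arm's size has SD √(60 × 0.5 × 0.5) = 3.9 and a 95% range of 22 to 38. That spread is chance in the allocation and carries nothing about willingness to enrol.

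**Fidelity and acceptability by arm.**

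| Measure | FB+SP (section 5.1, Box 1) | Augmented usual care (section 5.1) |
| --- | --- | --- |
| Checklist coverage | six structured sessions | nurse evaluation, brief counselling, up to 3 follow-up contacts; no checklist described |
| Intervention easy to administer and helpful | defined for FB+SP, though ease of administering belongs to providers | the term intervention is not defined for this arm |
| CSQ-8 (FU1, FU2) | can be asked | can be asked; Table 1 gives no arm restriction |
| Retention to 6 months | observed | observed |

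**Retention.** This outcome arises after randomisation and exists in both arms. Retention rates are not given, so these are assumptions. SE of the difference = √[2p(1−p)/30]:

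- both arms 0.90: √(0.18/30) = 0.077, 95% half-width 1.96 × 0.077 = 0.15
- both arms 0.80: √(0.32/30) = 0.103, 95% half-width 1.96 × 0.103 = 0.20

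The comparison is imprecise but informative.

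**Exit interviews.** Drawing 10 at random from 60, of whom 30 are controls, is hypergeometric:

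- expected controls = 10 × 30/60 = 5
- P(no controls) = C(30,10)/C(60,10) = 0.0004
- P(at least 3 controls) = 0.96

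The unrestricted wording and the section 5.5 wording would almost never give the same kind of sample.

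**The case against.** The strongest reply is that this is loose drafting. In the feasibility sentence, the reference to each arm may attach only to retention, and section 5.6 already lists planned against actual enrolment. The wording that models will be used as appropriate could be read as exempting one-arm measures. A statistical analysis plan may refine all of this. On interviews, section 5.5 is the more specific text, and the other sections may simply have omitted the arm.

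Part of this stands. The informative enrolment measure is already in the protocol, and the interview conflict causes harm only if section 5.5 is overlooked. But section 5.7 first applies the between-arm comparison to all three domains, and the qualifier reads as a choice between model types rather than an exemption. This is text the protocol sets down, not detail it leaves open. Three sections out of four give the wider interview sample.

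A reader might infer several stronger points that the document does not support:

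- That all the primary comparisons are empty. Retention is a valid contrast, and CSQ-8 satisfaction could be another, since controls also receive a study service.
- That the CSQ-8 has no analysis. The general provision for means and standard deviations covers it.
- That fidelity rests on too few counsellors. Their number is not given.
- That the stated standard errors need restating. They reproduce at n = 30 and refer to single proportions, not to a difference between arms.

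**Conclusion.** The point holds in limited form. Of the quantities named in section 5.7, number enrolled by arm is uninformative because allocation sets it, checklist fidelity by arm is undefined, and acceptability of the intervention is undefined for controls and partly put to the wrong respondent. Retention by arm is sound.

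Sections 5.3, 5.4 and 5.6 contradict section 5.5 on who is interviewed. The size, 5 controls expected among 10, assumes a simple random draw from 60 participants split 30 and 30, and applies only if the unrestricted wording is followed. The conclusions on enrolment and fidelity need no numerical assumption beyond the 1:1 design. The matter should be corrected because it concerns the primary outcomes, but it does not undermine the design or the sample size.

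**What to change.** In section 5.7:

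- Report enrolment as actual against planned, with reasons for non-enrolment, and make no arm comparison.
- Limit between-arm comparison to 6-month retention, given as a difference with a 95% confidence interval, and to the CSQ-8 if it is collected in both arms. State whether it is.
- Report checklist fidelity and FB+SP-specific acceptability within the FB+SP arm.
- Take ease of delivery from the staff interviews.

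In sections 5.3, 5.4 and 5.6, align the patient interview sample with section 5.5, so that the 10 patients are drawn from the 30 FB+SP participants.

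The cost is wording only: no added participants, visits or instruments. Leave the precision statement in section 5.5 unchanged.

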## Dissemination of Results

Local dissemination of evaluation results is critical to the success of this project. The goal is to publish all results and disseminate them at national and international scientific meetings. Results will also be distributed freely to colleagues across Malawi involved in the care of ALWH. This will include presentations to be given at UNC Project Malawi, the Malawi Ministry of Health Technical Working Groups, Kamuzu University of Health Sciences dissemination meetings, NHSRC meetings and through the UNCPM community advisory board. We will also present results at national and international conferences (e.g., IAS, CROI, Academy Health’s annual Conference on the Science of Dissemination and Implementation, the International Workshop on HIV & Adolescence, International Conference on HIV Treatment and Prevention Adherence). We will disseminate our results with the NHSRC. Abstracts presented at conferences will also be prepared for publication to disseminate results to the wider scientific community.

# ETHICAL CONCERNS

## Human Subjects

Safety considerations: Study staff will evaluate patients for safety who endorse any level of suicidal ideation whether or not they enroll in the study. Safety assessment results will be conveyed to the clinical team as appropriate for further follow-up according to the clinic’s standard operating procedures.

## Institutional Review Board

Prior to implementation of the formative research, all protocol materials will be reviewed by the University of Pennsylvania Institutional Review Board, in the U.S., and the Malawi National Health Sciences Research Committee (NHSRC) before any data collection or analysis occurs. The study will also be reviewed and informed by the existing community advisory board (CAB) of UNC Project in Malawi. The CAB reviewed first reviewed the study in July 2024. The CAB will provide ongoing review, providing feedback on the protocol and implementation. All research procedures will adhere to Malawian and US ethical standards for research involving human subjects.

## Confidentiality, Risks, and Risk Minimization

Risks of loss of confidentiality or social harms to participants will be minimized by 1) training of study staff in the ethical conduct of research; 2) strict protection of confidentiality and personal information; 3) close monitoring of social harms with appropriate IRB reporting.

All study data will be kept in a locked cabinet at UNC Project, where they will be maintained in a locked office accessible only to study staff. All data will be de-identified before analysis. Only the principal investigator, data entry personnel, and assigned data analysts will have access to the de-identified electronic study database. All study data will be destroyed 1 year after the completion of all study-related activities.

Discussing personal information: Data collection will include asking ALWH about their mental health. All data associates will be trained to keep all information confidential. Research assistants will be trained, and participants informed, that they can pause or discontinue a research interview at any time if they find the topic upsetting.

Data security: All study data, including interview guides, audio recordings of interviews, interview transcribes, and logbooks will be kept in a locked cabinet at the UNC Project data center, where they will be maintained in a locked office at UNC Project accessible only to the principal investigator. Interviews that are transcribed and computerized will be stored on the secure central server at UNC Project. For analysis purposes, data will be de-identified before coding and analysis. Only the principal investigator, data entry personnel, and assigned data analysts will have access to the de-identified electronic study database.

Preventing Discomfort: The surveys, counseling sessions, and peer support activities may cause discomfort for some participants. Efforts will be made to minimize this discomfort by assuring that participants are informed beforehand about the nature of the interaction and that the interaction is completed in a private setting. Participants will be informed that they have the right to decline participation in the study, to refuse to answer any questions, or to withdraw at any time. The consent form will also emphasize that personal information (and inclusion in the study based on HIV and suicidality) will be shared during focus groups and confidentiality cannot be assured.

Addressing Harms: Our overall goal is to protect the well-being of ALWH, thus if sexual or physical abuse is reported, we will ensure ALWH are referred to a local organization that deals with sexual abuse/violence so that the individual receives appropriate care or to a local social worker. If a study team member comes to believe that a participant is experiencing a crisis (which the participant may or may not recognize) they also may refer to local social workers for counseling or psychosocial support. Examples would include a participant who is having an extreme emotional reaction when discussing the challenges of living with HIV, or a participant whose behavior suggests possible undiagnosed mental illness. These revelations of harm are not common but may occur on a limited basis, necessitating that study protocols be in place to respond appropriately.

At each clinic from which we will recruit participants, we will identify a provider to act as the “clinic lead” for navigation services. This person is a chief point of contact for the study team. When a situation arises where study staff learns of a potential risk of harm to a participant, the following steps will be followed:

1. The study team member learning of the problem will immediately inform the PI.
2. If the participant is actively in distress and at the clinic, the study team member will refer the participant to the clinic lead (or, if the lead is not available, to another clinic provider) for immediate evaluation.
3. If the participant is actively in distress and not at the health center, the study team member will offer to meet the participant and accompanying them to the health facility for immediate referral.
4. If the participant is not actively in distress, then the study investigators, project manager, and other appropriate project supervisory staff will develop a plan for referring the participant to the clinic lead. As appropriate, the project team may consult the clinic lead in developing the plan. (All consent forms will note that investigators may need to break confidentiality when there is a threat of harm to self or others.) The timing and most appropriate means of effecting a referral will be dependent on the nature of the problem. For example, if a participant reports child abuse in the home, then it would be necessary to involve appropriate social services to investigate the problem. By contrast, if a participant reports that she/he is facing ongoing (but not life threatening) emotional abuse from a partner, then it may make more sense for the navigator to first approach the participant and encourage her/him to meet with a clinic provider or with other social support services in the area.
5. Study investigators will inform all governing IRBs of the incident and update the IRBs as necessary on the outcomes of efforts to intercede and resolve the harm.

Response to suicidal thoughts, ideation or behaviors: For participants who indicate any SIBs during research assessments, IDIs or FGDs, we will follow a suicide risk assessment and response protocol that we have previously deployed in several prior studies in Malawi.^17^ Using this structured protocol, the research assistant will assess suicide risk using the Suicide Risk Assessment Protocol (SRAP) questions.^17^ These questions will allow for differentiation between passive and active suicidal thoughts and assessment of suicide risk factors to further classify active suicidal thoughts into low, medium, or high risk. All participants reporting SIBs will see a clinician that same day. Following the protocol, the research staff will accompany the participant to a clinician with the results of the risk assessment for the clinician to then decide on appropriate further clinical response following the clinic’s standard safety procedures. All clinical staff at the study sites have been trained on suicide risk management, and are able to provide supportive counseling, review a safety plan, provide medication management, and refer to the clinic’s psychiatric nurse as necessary. For acute cases or crises, all clinic staff are trained to refer to the psychiatric unit at Bwaila Hospital in Lilongwe District. Additionally, we will train a study nurse who will be available on-site to assist the existing clinical staff, provide mental health evaluation, brief supportive counseling, information, education and support on SIBs as needed. For acute cases or crises, the study nurse will facilitate referral to the psychiatric unit at Bwaila Hospital. The study nurse will have up to 3 follow-up contacts with all participants reporting SIBs to assess whether they have followed up on recommended referrals or treatment plans and to assess whether any further outreach is needed.

Response intimate partner violence: For enrolled participants who indicate any recent sexual or physical violence by an intimate partner on the participant survey section on intimate partner violence or who otherwise indicate a potentially unsafe home situation, the study team will follow a IPV safety assessment and response protocol that we have deployed successfully in prior studies in Malawi. All participating health facilities have a One-Stop Centre with one or more behavioral health professionals on staff who can discuss reporting and support options with an affected individual. In Malawi, reports of intimate partner violence are handled by a designated Victim Support Unit of the local police department. Our safety protocol guides our study team member to discuss with the participant the available support services and options, including going to the facility’s One Stop Centre to meet with a behavioral health professional and connecting with the local police department’s Victim Support Unit. Whether the participant takes any action will be left at the discretion of the participant since reporting can carry its own risks. When possible, the study team member will provide a warm handoff to a facility clinician to further discuss the participant’s situation and options. If the participant chooses not to meet with a clinician, the study team member will ask the participant to sign the study safety assessment form indicating that they are declining to meet with a clinician.

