FB problem-solving counseling will begin on the second session. The first FB session includes three components called Opening the Mind, Uplifting, and Strengthening, with subsequent sessions building on the first. Opening the Mind refers to the therapeutic process by which, through asking questions, clients are encouraged to open their minds to identify their problems, choose one to work on, identify a feasible solution, and agree on an action plan through an iterative process guided by the counselor. Each structured session lasts 30-45 minutes and will be conducted in a private clinic room in the participant’s local language (Chichewa). No specific retention support will be provided, but participants may identify barriers to engagement in HIV care to address during their counseling session. After 4 sessions of individual therapy, the counselor can refer participants not improving or with suicidal ideation to a supervisor trained in mental health to reassess and manage the case. Case management may include additional counseling or pharmacotherapy, at the discretion of the managing clinician.

Additionally, adolescents will be offered structure peer support via in person group meetings to facilitate engagement in care for ALWH and support SIBS reduction, as is now standard with the existing adolescent-FB package.^53^ Peer supporters will be mature young adults (aged 18-21) who have completed secondary school, are openly living with HIV, and motivated to work with adolescents. The counselors must be willing to maintain participant and colleague confidentiality and sign a confidentiality agreement. Peer Supporters will be trained to deliver youth-friendly group sessions related to HIV care. The content of the 6 peer support sessions includes: Mental Health and HIV, Status Communication, Adherence and Viral Load Testing, Secondary Prevention (Sex and Relationships), Stigma, and Planning for the Future. The 6 sessions will be delivered monthly over 6 months and last 90 minutes each. The group sessions will be in a private space in the clinic in the participant’s local language (Chichewa).

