## Informed Consent

In this study, we are seeking to enroll ALWH 13-19 years to participate. ALWH who are 18 years or older will provide consent for themselves. ALWH 13-17 years will provide assent and will have an authorized adult over 18 years provide consent for them prior to participation. The authorized adult can be a parent, a legal guardian, or someone designated as an authorized representative. The research study will be described briefly to all adolescents accessing ART services at Area 18, Area 25, or Kawale Health Centers in Lilongwe while they wait in the reception area. Once a participant is determined to be eligible for the study a trained interviewer will complete an informed consent process with each participant in their native language, Chichewa. During the informed consent process, the counselor will describe the procedures to be followed, the risks and benefits of participation, the duration of participation, and the steps taken to protect participant’s confidentiality, particularly with respect to keeping all personal and private information (such as HIV, depression status, and SIBs) private to the extent possible by the study team. The counselor will also emphasize that the consent form says that confidentiality of sensitive information cannot be assured during focus groups. Illiterate participants may sign the consent form via thumbprint, in the presence of an impartial witness. Any questions or concerns about privacy will be answered by the counselor or referred to the PI, who will address them. In order to provide protection to this group, we will have rigorous trainings of research staff. We will teach staff to be sure that there is an adequate assessment of understanding. Staff will ensure participants fully understand the content, and time for questions will be encouraged, and answered honestly. We will be clear that refusals will not compromise access to services in any way. We will follow a work practice guideline of when mandatory reporting is required and the best methods to do so, e.g. evidence of exploitation or sexual abuse. Additionally, both sites will adequately map out referrals services to deal with a range of potential needs. All ALWH who screen positive for depression or SIBs will be referred to outpatient psychiatry services that are currently available and staffed by master’s level nursing staff that can prescribe antidepressant medications. ALWH reporting SIBs who choose not to participate will be referred to a mental health provider. Written informed consent will be obtained from each participant and participants will be provided with a copy of their informed consent forms if they are willing to receive it. Study staff will document the informed consent process.

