## Budget Justification (USD)

Personnel

Two Research Assistants in Malawi ($10,800 - 100% effort for 12.0 months) – Two research assistants in Malawi will be hired and trained to assist with the pilot trial.  $450 salary/month x 12 months x 2 research assistants = $10,800

Additionally, we will hire a research nurse half-time to support SIBs management and provide follow-up to ensure appropriate referrals and/or treatment have been implemented. $450 salary/month @ 50% effort x 6 months = $2,700

Total Personnel Costs $ 13,500.

Compensation for Study Participants and Guardians

Travel Reimbursement for study visits for participants ($3,600) – A total of 60 participants will be included in our proposed aims. Each participant will receive $10 per study visit (6 per participant) for travel reimbursement.

Travel Reimbursement for enrollment visit for guardians ($600) – Each guardian (for 60 adolescent participants aged 13-19) will receive $10 for travel reimbursement for the initial enrollment visit.

Travel Reimbursement for counseling/peer support sessions for participants ($1,800) – Each participant will receive $5 for travel reimbursement for each counseling or peer support session. 30 participants will receive 6 counseling sessions and 6 peer support sessions (12 sessions total).

Travel Reimbursement for exit interviews ($200) – Each participant will receive $10 for travel reimbursement for each exit interview. 10 adolescent participants and 10 healthcare facility staff will participate in the exit interviews.

Total Compensation for Study Participants and Guardians Costs $ 6,200.00

OTHER RESEARCH COSTS

HIV Testing ($5400) – We will collect viral loads at 45 USD per test for all 60 participants at enrollment and 6 months.

Translation and Transcription Fees ($200) – All study materials including informed consent forms, surveys, and interview guides will be translated into Chichewa, the local language in Lilongwe, Malawi. Translation fees $200.

Malawi IRB Fee ($150) – All research in Malawi must receive ethical approval from the National Health Science Research Committee, which charges a $150 fee to review all applications for ethical approval.

Total Other Research Costs $350

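### The consent warning on confidentiality names focus groups, which the trial does not describe, and not the six peer-support group sessions that it does

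*Protocol*

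**What the plan says.** Two places in the protocol prescribe a warning about the limits of confidentiality. Section 6.3, under Preventing Discomfort, says the consent form will emphasise that "personal information (and inclusion in the study based on HIV and suicidality) will be shared during focus groups and confidentiality cannot be assured". Section 6.6 turns this into an instruction to staff: "The counselor will also emphasize that the consent form says that confidentiality of sensitive information cannot be assured during focus groups".

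Focus groups appear in one other place, as an abbreviation in the suicide-response text of section 6.3: "For participants who indicate any SIBs during research assessments, IDIs or FGDs, we will follow a suicide risk assessment and response protocol".

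The group activity that the protocol does describe is in section 5.1. Adolescents in the FB+SP arm are offered in-person group peer support: "The 6 sessions will be delivered monthly over 6 months and last 90 minutes each". The topics include HIV and mental health, communicating one's status, stigma, and sex and relationships. Three safeguards bear on these sessions:

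- a private space in the clinic (section 5.1);
- a signed undertaking from those delivering sessions: "The counselors must be willing to maintain participant and colleague confidentiality and sign a confidentiality agreement" (section 5.1);
- information in advance: "Efforts will be made to minimize this discomfort by assuring that participants are informed beforehand about the nature of the interaction" (section 6.3).

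**The concern.** The sponsor saw that a group setting can reveal a participant's HIV status and suicidality, and it wrote a warning for that risk. The warning is attached to an activity the trial does not describe. The group activity the trial does offer is left out of it.

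What is at stake is informed consent and assent. Participants are aged 13 to 19, live with HIV and report current or past suicidal ideation or behaviour. The protocol's own background says that suicide attempts are a criminal offence in Malawi and that stigma is widespread. Whether other young people in the room are bound to keep what they learn to themselves is material to an adolescent's decision to attend and to a guardian's decision to allow it. Nothing statistical depends on this point.

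**Working it through.** The plan gives no figure to reproduce. The check is a comparison of texts, followed by a count of exposure.

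**Step 1. Is a focus group described anywhere?**

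| Place in protocol | What it describes |
| --- | --- |
| 5.1 Design | Individual counseling, group peer support, augmented usual care |
| 5.3 and 5.4 Population, sampling | Exit interviews with 10 adolescents and 10 staff |
| 5.5 Sample size | The same interviews, 10 and 10 |
| 5.6 Data collection, Table 1 | Semi-structured or in-depth interviews, surveys, clinic data, viral load |
| 5.7 Analysis | Qualitative analysis of exit interviews |
| 8.0 Budget | Travel for exit interviews (10 adolescents, 10 staff); no focus-group line |

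The listed budget lines leave no unlisted activity. In dollars, 10,800 + 2,700 + 3,600 + 600 + 1,800 + 200 + 5,400 + 200 + 150 = 25,450, which is the stated total before the 10% fee.

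Focus groups described in the methodology or budget: 0. The term or its abbreviation occurs in three sentences, all in the ethics section: two in 6.3 and one in 6.6. None has a sample, a timing or a procedure behind it. The wording may be carried over from earlier work, since section 5.7 refers to an Aim 1 and section 6.2 to formative research. The protocol does not confirm this.

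**Step 2. Does either warning reach the peer-support sessions?** The Preventing Discomfort paragraph in 6.3 names peer support in its first sentence, as a possible source of discomfort. Its last sentence, on confidentiality, uses the other term. Section 6.6 likewise says only that "confidentiality of sensitive information cannot be assured during focus groups". Peer support is named in neither warning.

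**Step 3. Do the other safeguards fill the gap?**

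- A private room keeps out people who are not attending. It does not restrain those who are.
- The signed agreement binds those delivering sessions. No equivalent is stated for attendees.
- Advance information is offered as a way to reduce discomfort and states no limit on confidentiality.

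None of the three addresses disclosure by a fellow attendee.

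**Step 4. Exposure.** Inputs from the budget and its justification: 30 participants, 6 counseling and 6 peer-support sessions each, $5 per session.

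- All FB+SP sessions: 30 x (6 + 6) = 360. At $5 each this is $1,800, which matches the budget line.
- Peer-support attendances: 30 x 6 = 180.
- Share: 180 / 360 = 50%.
- Usual care: 0 group attendances.

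These counts assume that everyone attends every session.

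**The case against.** The strongest reply is that the consent and assent forms are the operative documents, and they were not available. If they name the peer-support sessions, what remains is a wrong noun in the protocol. This stands as a limit on what can be said about participants. It does not rescue the text: section 6.6 has staff stress what the form says about focus groups, so the protocol expects the form to carry that wording. If the form differs, the two documents disagree and one needs correcting.

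A second reply is that focus groups is a loose label for the peer groups, because the sentence closes a paragraph that opens by mentioning peer support. That is possible, but the protocol nowhere says so and uses both terms in that one paragraph for different purposes.

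Third, section 6.6 requires staff to describe procedures and risks in general, check understanding, and promise privacy only as far as the study team can provide it. Peer support is also optional, participants may withdraw, social harms are monitored and reported, and the community advisory board reviews implementation. These points lower the stakes. None tells an adolescent that other attendees may disclose.

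Finally, the session topics concern HIV more than suicide attempts, so disclosure of HIV status is the more direct worry and criminalisation the less direct one. That is fair. The sponsor's own warning nonetheless covers both HIV and suicidality.

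**Conclusion.** The concern holds: the warning is wrong as written. It names an activity with no description in the methodology or budget and omits the one group setting described there. The reach is up to 180 group attendances among 30 adolescents, which is a ceiling at full attendance and says nothing about how often disclosure would occur or how many would be misinformed. The conclusion about the protocol text is firm. The consequence for participants depends on the wording of the consent and assent forms, which is unknown here. No endpoint, sample size or analysis changes. Because the sentence in section 6.6 is an instruction to staff working with a vulnerable group, it should be corrected.

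**What to change.** - In sections 6.3 and 6.6, make the warning name the peer-support sessions. Suggested wording: *personal information may be shared during peer-support group sessions, and confidentiality on the part of other attendees cannot be assured*.
- If no focus groups are planned, delete the term from 6.3 and 6.6, and delete FGDs from the suicide-response text in 6.3. If any are planned, keep the term alongside the peer-support sessions.
- Check that the consent and assent forms carry the same wording.

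The cost is an edit to three sentences and a check of the forms, submitted for IRB and NHSRC approval under section 6.9. No new data, visits or staff are needed.
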